## Measurement and reporting of participant compliance to treatment protocol:

Session attendance will be measured as a marker of adherence, with a benchmark of attending at least 75% of the coaching/assessment sessions for both index participants (11 out of 14) and social network members (3 out of 4). 'Treatment (intervention) fidelity' will be assessed in three ways. The first is a checklist in REDCAP that the coach will complete at the end of each session. This checklist will also serve as a reminder to the coach about the active ingredients to be delivered during the session. The second method is a monthly review of a random sampling of 10% of the coaching sessions. Points will be given for each required treatment element delivered correctly and subtracted for any contamination elements. If the average fidelity falls below 90%, the coach will be retrained. The third is by each tracking the session duration in minutes. The coach will assess enactment fidelity at the beginning of each coaching session using a simple yes/no checklist. This data will be reviewed in bi-weekly team meetings (study coordinator, PI and interventionists) and reviewed by the safety officer bi-annually. If the safety officer has concerns about whether intervention fidelity has reached a level that might inhibit the ability of the study to test its primary hypotheses, she will suggest a conference call for study investigators to discuss methods for improving study adherence.

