# 1. Protocol Summary

Full Title: Reducing OBesity Using Social Ties (ROBUST): Randomized Controlled Trial Short Title: ROBUST- RCT

Clinical Phase: III

Principal Investigator: [name], MS

**Study Description:** Randomized controlled trial comparing two behavioral weight-loss interventions; a social-network enhanced lifestyle intervention (Intervention group) and an individual level lifestyle intervention (Control group), among Black and Hispanic adults with obesity over the course of 24 weeks. This study aims to test the feasibility and acceptability reforming interpersonal barriers and addressing social network barriers to behavior change, by engaging social network members in a lifestyle intervention for weight loss compared to the lifestyle intervention alone.

**Sample Size:** *N=* *66 (Intervention index participants)*

*N=132 (Intervention Social Network members)*

*N= 66 (Control participants)*

*N=264 (Total Sample Size)*

**Enrollment:** In the intervention group, this study will enroll 66 index participants and 132 social network member subjects. In the control group, this study will enroll up to 66 index participants.

**Study Population:** Individuals who self-identify as Non-Hispanic Black or Hispanic adults 18 years of age or older with a calculated BMI ≥ 30 kg/m2

**Enrollment Period:** *24 weeks*

**Study Design:** Randomized controlled trial comparing a social-network enhanced lifestyle (intervention group) to an individual-level lifestyle intervention (control group). Subjects in both arms (n=66 each) will receive the same number of behavioral coaching sessions (15 total) with four sessions conducted in person (baseline, week 8, week 16, and week 24), and the remaining 11 sessions conducted virtually. Subjects randomized to the social network intervention will nominate up to a maximum of two members of their social network (n=132) who will also be consented at baseline, complete a brief baseline interview, and attend the virtual coaching sessions with the randomized subject at weeks 3, 5, and 15. The social network members will also complete a close-out study interview at week 24.

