## 2.5 Correlative Studies Background

**Not applicable**

# 3. Study Design

## 3.1 Overall Design

This randomized controlled trial comparing a social-network enhanced lifestyle intervention (intervention group) to an individual-level lifestyle intervention (control group) will be conducted among 132 adult individuals who self-identify as Black or Hispanic with obesity (BMI ≥ 30 kg/m2). The hypothesis being tested is that the multi-component social-network enhanced lifestyle intervention will be feasible, acceptable, and lead to positive change in key social network processes (communal coping, social norms, and affect) that will reduce established interpersonal barriers (social undermining, unhealthy social norms, and interpersonal conflict) to weight-loss. 132 index participants will be recruited and evenly randomized to either the social network intervention group or the control group. Both groups will be followed over 24 weeks (6 months), completing virtual coaching sessions on zoom, along with three in person dietary assessments and weigh-ins. Individuals randomized to the intervention will nominate up to two personal social network members who will participate with the index participants in three virtual communication skills sessions.

[figure not shown]

##

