### **Visit 1 (Intake; Week 0)**

### Review accuracy of completed baseline survey (10 minutes)

### Conduct anthropometrics (15 minutes)

### Conduct Social Network Survey (15 minutes)

### Set up Program Equipment & set coaching schedule (45 minutes)

### **Visit 2 (Track your food and physical activity; Week 1)**

- - - - 1. Check in (5 minutes)
        2. Review self-regulations skills (10 minutes)
        3. Review workbook lesson (30 minutes)
        4. Homework & set new/or revise SMART Goal (5 minutes)

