## 7.11 Measures to Minimize Bias: Randomization and Blinding

Index participants will be randomized after completion of the social network interview either to the ROBUST intervention or lifestyle intervention, using a random number generator. All index participants, regardless of randomization group, will complete a social network interview to characterize their personal network prior to randomization. The same social network interview will be conducted at 24 weeks. All participants will also receive the same number of coaching sessions, as shown in **Table 1**. They will attend four sessions in person (baseline, week 8, week 16, and week 24), and the remaining 11 sessions will be conducted as a virtual visit. The in-person visits will occur at the Weill Cornell Clinical and Translational Science Center's dedicated research facility. During the in-person sessions, the participant will receive 1:1 dietary counseling with a registered dietician who has been trained on the study protocol. The study research staff complete anthropometric measurements (height, weight, and body composition). Participants randomized to the intervention group will be expected to attend virtual visits at weeks 3, 5, and 15 with their social network member.

Consenting of study participants as well as all study assessments (i.e. baseline, 8 ,16 & 24 weeks) will be conducted by an assessor who is not responsible or involved in the delivery of the coaching sessions, dietary counseling or communication skills sessions. While the study PI & co-investigators will be blinded, the same will not be possible for the trained coach delivering the intervention. Due to budget limitations, having two coaches (i.e. one for the control group and for the intervention group) is not feasible. Since the communication skills training sessions are designed to occur between the index participant and consented social network members, the implication of contamination is reduced as control group participants will not have any consented social network members participating in the study.

*.*

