## 12.1 Study Design/Endpoints

This randomized controlled trial will use the following primary endpoints as the promising range to justify further testing of this agent:

- At least 75% attendance rate for the participant and their network members in their respective behavioral coaching sessions.
- 80% of participants or more to have at least one network member engage in the study.
- 85% of participants and their network members or more to complete the final study assessment.

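### The monitoring plan scores network-member attendance as 3 of 4 contacts, but members have only three coaching sessions, so a member at 66.7% can meet the 75% benchmark

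*Protocol*

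**What the plan says.** Section 12.1 makes the following part of the range that would justify further testing: "At least 75% attendance rate for the participant and their network members in their respective behavioral coaching sessions". Section 1.2.4 gives the same endpoint. Section 12.4.1 then calculates the share of coaching sessions attended, separately for index participants and for network members, without giving denominators.

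**Network members.** Section 3.1 gives them "three virtual communication skills sessions". Sections 1 and 7.11 place these at weeks 3, 5 and 15. Members also have two assessment contacts, at baseline and at week 24, which Section 1 describes as interviews and Appendix B as surveys.

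**Index participants.** Section 1 says that both arms "will receive the same number of behavioral coaching sessions (15 total) with four sessions conducted in person". Section 7.11 agrees: after four in-person sessions, "the remaining 11 sessions will be conducted as a virtual visit". The visit list in Section 6.1.2 also has 15 entries, starting with "Visit 1 (Intake; Week 0".

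**Monitoring plan.** In Section 15, the part on compliance with the treatment protocol treats attendance as a marker of adherence, "with a benchmark of attending at least 75% of the coaching/assessment sessions", and gives the counts "for both index participants (11 out of 14) and social network members (3 out of 4".

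**The concern.** The same 75%, for the same two groups, is applied to different sets of contacts. Sections 1.2.4, 12.1 and 12.4.1 count coaching sessions. The monitoring plan counts coaching and assessment contacts, with denominators of 14 and 4.

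No single stated rule gives that pair. The sessions that Section 1 calls coaching number 15 for index participants and 3 for members. Adding every assessment gives 15 and 5. Fourteen fits if the week-0 intake is dropped. Four fits only if one of the members' two assessments is counted and the other is not.

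The member count matters most. The three joint sessions are what distinguishes the intervention from the control, and their attendance is one of the criteria for going on to a further trial. Progress reports under the monitoring plan could show the benchmark as met on data that miss the endpoint. If the fourth contact is the week-24 close-out, the same event also counts towards the third primary endpoint, completion of the final assessment.

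**Working it through.** **1. The plan's own counts.** The fewest contacts that reach 75% of n is 0.75n rounded up.
- n = 14: 0.75 × 14 = 10.5, so 11 (11/14 = 78.6%).
- n = 4: 0.75 × 4 = 3 (75.0%).

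Both stated counts follow from their denominators. The question is which contacts make up the denominators.

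**2. Counts on the sessions described elsewhere.**
- Index, weeks 0, 1, 2, 3, 4, 5, 7, 8, 9, 11, 13, 15, 16, 20 and 24: n = 15, 0.75 × 15 = 11.25, so 12 (80.0%).
- Members, weeks 3, 5 and 15: n = 3, 0.75 × 3 = 2.25, so 3 (100%); 2/3 = 66.7% fails.
- Members with both assessments added: n = 5, 0.75 × 5 = 3.75, so 4 (80.0%).

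**3. One member.** Across all combinations of 0 to 3 coaching sessions with the fourth contact attended or missed, the two rules disagree in one case only: two coaching sessions plus the fourth contact. That is 2/3 = 66.7% (fail) against 3/4 = 75% (pass).

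**4. Members as a group mean.** Let r be mean attendance over the three sessions and c the share who attend the fourth contact. The four-contact mean is (3r + c)/4, which reaches 0.75 when r ≥ (3 − c)/3.
- c = 1 (fourth contact always attended): r ≥ 2/3 = 66.7%.
- c = 0.85 (assumed close-out completion, set at the trial's own target): r ≥ 2.15/3 = 71.7%. For example, r = 72% gives (2.16 + 0.85)/4 = 75.25%.

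From these values up to just under 75%, the data pass on four contacts and fail on three. If c were below 0.75, the discrepancy would run the other way.

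**5. Per-person illustration.** Assume each session is attended independently with probability 0.80.
- 3 of 3: 0.8³ = 0.512.
- At least 3 of 4, fourth contact also at 0.80: 4 × 0.8³ × 0.2 + 0.8⁴ = 0.819.
- At least 3 of 4, fourth contact certain, so at least 2 of 3 coaching sessions: 3 × 0.8² × 0.2 + 0.8³ = 0.896.

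**6. Index participants, if 14 means the 15 visits without intake.** Section 7.11 randomizes after the social network interview, and Section 6.1.2 places the network survey at Visit 1. On that reading every randomized participant has attended intake.
- 11/14 becomes 12/15 = 80.0%: pass on both.
- 10/14 = 71.4% becomes 11/15 = 73.3%: fail on both.

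No individual changes status. For a group mean m over the 14, (14m + 1)/15 ≥ 0.75 needs m ≥ 10.25/14 = 73.2%. A mean from 73.2% to just under 75% fails on 14 and passes on 15.

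**7. Index participants, if the omitted visit is week 24.** Someone who attends 11 of the other 14 and misses week 24 scores 11/14 = 78.6% (pass) and 11/15 = 73.3% (fail).

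**The case against.** The strongest reply is that the monitoring plan does not define the endpoint. It describes an adherence marker, says openly that assessments are included, and leaves Section 12 to govern the analysis. An analyst who follows Section 12.4.1 would count coaching sessions only. This stands as far as it goes: a reader might infer that the primary endpoint itself is defined on 14 and 4, and the protocol does not say so. But the monitoring plan uses the endpoint's own percentage for the same two groups and is the only place with counts. Its wording shows where a fourth member contact could come from, but not which of two assessments it is.

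A reader might also infer that the index benchmark falls short because 11/15 is 73.3%. The documents do not support that if 14 leaves out the intake, as the visit list suggests. Someone with 11 of 15 including intake has 10 of 14 and fails both ways.

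The contrast of 51% with 90% of members should not be read as the size of the problem. It takes the most favourable fourth contact and a per-person rule. With the fourth contact also at 80% the figure is 82%. As a group mean, 80% coaching attendance passes on three sessions, and on four it gives 80% to 85%.

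Finally, whether 75% is a mean or a per-person criterion can properly be settled in a statistical analysis plan and is not held against the protocol here.

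**Conclusion.** The concern holds for network members. The protocol applies one 75% criterion to three coaching sessions in some sections and to four contacts in another, and the fourth contact is not identified. A member at 66.7% coaching attendance can meet the monitoring benchmark. As a group result, the conclusion changes only if mean coaching attendance lies between 66.7% and just under 75% (fourth contact attended by all), or between 71.7% and just under 75% (85% close-out completion, an assumption). Outside these bands the choice of count does not change the group result in those two cases.

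For index participants the mismatch is minor. On the intake reading no individual is reclassified, and only a group mean of 73.2% to just under 75% over the 14 sessions is affected. This is a conflict between sections, not an arithmetic error: 11 of 14 and 3 of 4 are correct minimum counts for their own denominators.

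**What to change.** Use one list of countable sessions per role in Sections 1.2.4, 12.1 and 12.4.1 and in the monitoring plan.

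- **Network members:** count only the three communication-skills sessions, remove the 3-of-4 benchmark, and judge mean attendance over those sessions against 75%. A mean is the workable unit, because one person can reach 75% of three sessions only by attending all three.
- **Index participants:** state whether the week-0 intake counts, and use the same denominator, 14 or 15, throughout.

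The cost is wording only. The member benchmark becomes slightly less favourable than the present 3 of 4.

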### **6.1.2 Treatment Phase**

Eligible participants will be randomly assigned to the social network intervention or control groups in a 1:1 ratio using a numerical randomization scheme developed by the statistical team. Following randomization, participants that are randomized to the social network intervention group will complete 3 in person communication skills sessions with their social network members during weeks 3, 5, and 15. Instead of completing communication skills sessions, participants randomized to the control group will complete regular virtual lifestyle coaching sessions with the study team that consists of the following topics: Keep your health healthy (week 3), Eat well away from home (week 5), and Social Cues (Week 15). All other sessions will focus on the topics below and will be the same across both treatment groups.

Note: The weeks that are not listed in the treatment phase below are weeks that will be treatment breaks.

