## 7.5 Product Storage and Stability

**Not Applicable**

## 7.6 Preparation

**Not applicable**

## 7.7 Dosing and Administration

Participants receiving the social network intervention will complete communication skills sessions during weeks 3, 5, and 15 of the study. Participants in the control group will complete regular discussion sessions during week 3,5, and 15 of the study which will consist of the following topics: Move those muscles, Keys to health eating out, and social cues, respectively. Those who continue in the study will only receive each session one time.

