## 12.3 Stratification Factors

**Not applicable**

## 12.4 Analysis of Endpoints

### **12.4.1 Analysis of Primary Endpoints**

Feasibility will be assessed based on rates of recruitment, study conduct (intervention and enactment fidelity), retention and acceptability of the study. Descriptive statistics will be used to summarize recruitment rates for clinical and faith-based organizations separately. The screening-to-enrollment (STE) ratio will be defined and calculated as the proportion of people who consented to those for whom screening was attempted. The reasons for declining participation will be grouped into categories and the proportion described.

Adherence to several aspects (session attendance, dietary, physical activity and self-weights) of the intervention will be tracked. The proportion of coaching sessions attended by the index participant and social network member across the 24 weeks will be calculated separately. Additionally, a tally of each self-regulation behavior (total # of days weighing, total # of days self-monitoring dietary intake, & total # of days wearing fitness tracker) will be summarized.

Treatment fidelity will be summarized as an average of the proportion of treatment elements delivered correctly. A correlation (Pearson) between the self-reported checklist and objectively measured checklist will be conducted. The retention rate will be defined as the proportion of participants who complete the 24-week assessment among those who completed the baseline assessment. Sample sizes and the proportion of missing data will be calculated for each measure collected as baseline, follow-up visits and study completion. Chi-Squared tests (or Fisher's exact tests) and two-independent-sample t-tests (or Wilcoxon rank-sum tests) will be used, as appropriate, to examine whether baseline characteristics predict retention and to identify differences in dropout rates between the intervention and control group. The qualitative satisfaction data will be content analyzed. Two study personnel will generate a priori codes corresponding to the interview guide (e.g., reactions to enrolling network members). One study personnel will apply the coding scheme to each interview summary, and then the two will formalize agreement or disagreement regarding the derived codes.

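### The single pooled 90% fidelity trigger is insensitive to, and does not isolate, poor delivery of the communication-skills sessions, and a Pearson correlation alone cannot show that the coach's checklist is accurate

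*Protocol*

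**What the plan says.** Section 15, under participant compliance, measures treatment fidelity in three ways: a checklist the coach completes after every session, a sampled review, and session duration. The sampled review is described thus: "The second method is a monthly review of a random sampling of 10% of the coaching sessions". Its scoring is: "Points will be given for each required treatment element delivered correctly and subtracted for any contamination elements". The action rule is: "If the average fidelity falls below 90%, the coach will be retrained". The text does not say whether that average is monthly or cumulative, and it sets no rule by arm or session type.

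Section 12.4.1 gives the analysis: "Treatment fidelity will be summarized as an average of the proportion of treatment elements delivered correctly", followed by "A correlation (Pearson) between the self-reported checklist and objectively measured checklist will be conducted".

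Section 6.1.2 states that every session other than weeks 3, 5 and 15 is the same in both arms. Section 7.11 says that "having two coaches (i.e. one for the control group and for the intervention group) is not feasible", so one unblinded coach serves both arms.

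The sessions at weeks 3, 5 and 15 are not described consistently. Section 6.1.2 says intervention participants "will complete 3 in person communication skills sessions with their social network members during weeks 3, 5, and 15", whereas the section 1 study design, section 3.1 and section 7.11 make those sessions virtual. Section 7.7 lists the control topics as "Move those muscles, Keys to health eating out, and social cues". For weeks 3 and 5 these differ from section 6.1.2 and from the Visit 4 and Visit 6 headings; week 15 agrees.

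**The concern.** Fidelity is part of the primary feasibility assessment, and section 15 says the trial is also meant to supply estimates for a larger one. If the two arms end up alike, the reader must be able to tell an intervention that does not work from one that was not delivered. That depends on delivery of the communication-skills sessions in one arm and on the absence of their content in the other. A single average over all coaching sessions is dominated by lifestyle sessions common to both arms, so it can look satisfactory while the component under test is largely missing.

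The reason to compare the coach's checklist with an objective one is to learn whether the coach's record can be trusted. A correlation answers a different question: whether the two scores rise and fall together.

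**Working it through.** The protocol derives no figure for the 10% sample, the 90% line or the correlation, so there is none to reproduce.

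**Inputs from the protocol.** 132 index participants, 66 per arm (section 3.1); 15 sessions each (sections 1 and 7.11), although the attendance benchmark in section 15 uses 14; 3 communication-skills sessions per intervention participant (section 7.7); accrual of 8 per month (section 12.2).

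**Assumptions, not in the protocol.** Fidelity in the other sessions f0 (98% as the main case, 92% to 100% as the range); for the simulation, 10 independently scored elements per session and no dropout.

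**1. Share of sessions.** Communication-skills sessions: 66 × 3 = 198. With k sessions per participant, s = 198 / (132 × k).
- k = 15: 198 / 1,980 = 10.0%
- k = 14: 198 / 1,848 = 10.7%
- k = 11 (virtual only): 198 / 1,452 = 13.6%
- k = 10 (intake, dietary counselling and close-out visits excluded): 198 / 1,320 = 15.0%

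**2. Pooled average.** Average = (1 − s) × f0 + s × fc, where fc is communication-skills fidelity. At fc = 50% and f0 = 98%:
- s = 10%: 0.90 × 0.98 + 0.10 × 0.50 = 93.2%
- s = 15%: 0.85 × 0.98 + 0.15 × 0.50 = 90.8%

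Neither is below 90%. Setting the average to 90% gives the break-even fc = (0.90 − (1 − s) × f0) / s:

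| f0 | s = 10% | s = 15% |
|---|---|---|
| 100% | 0% | 33% |
| 98% | 18% | 45% |
| 95% | 45% | 62% |
| 92% | 72% | 79% |

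**3. Monthly average.** A simulation used 8 accruals per month, a 10% sample each month, k = 15 or 11, and f0 = 98% unless stated. About 7 to 9 sessions are reviewed per month, about 0.9 of them communication-skills; 39% to 43% of months contain none.
- fc = 50%: a given month triggers with probability 0.20 to 0.31, and at least one month in the trial with probability about 1.00. Treating months as alike, the mean wait is about 1/0.31 to 1/0.20, or 3 to 5 months.
- fc = 70%: 0.06 to 0.13 per month and 0.77 to 0.96 over the trial; mean wait about 1/0.13 to 1/0.06, or 8 to 17 months.
- Every session type at 95%: at least one trigger still occurs with probability 0.39 to 0.47.
- Cumulative average instead, fc = 50%: flagged with probability 0.00 to 0.16.

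**4. Communication-skills sessions as their own stratum.** With n sessions of 10 elements, the trigger probability is P(Binomial(10n, fc) < 9n).
- n = 10: about 1.00 at fc = 50% or 70%; 0.90 at 85%; 0.01 at 95%.
- n = 20: 0.97 at 85%; 0.001 at 95%.

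A 10% sample yields about 0.10 × 198 = 19.8 such sessions over the whole trial (95% range 12 to 28).

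**5. Pearson correlation.** If the coach's score is y = a + b·x with b > 0, where x is the reviewer's score, then r = 1 whatever a and b are. For a constant 15-point over-report and an assumed SD of 6 points, Lin's concordance is 2 × 36 / (36 + 36 + 15²) = 72 / 297 = 0.24, while r = 1.00.

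**The case against.** Several points on the other side have force.

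- **Denominator.** Retraining concerns the coach, so coach-led sessions are a natural base. Section 15's adverse-event text lists nine routine coaching weeks. On that base s = 198 / 1,188 = 16.7%, and the break-even at f0 = 98% is 50%. Dilution persists, but it is milder than at 10%.
- **Total failure.** A reader might infer that the rule could never detect failure, since zero delivery with perfect delivery elsewhere averages exactly 90.0%. That holds only at 15 sessions; at 14 the average is 0.893 and retraining follows. It also needs a pooled or cumulative average. A monthly average would very probably trip at some point.
- **Sampling.** The text says random, not simple random, and an operational document could stratify. The stated trigger is nonetheless one average.
- **Other checks.** Every session has a coach checklist and a recorded duration, enactment is checked, the team reviews fortnightly and the safety officer twice a year. Appendix B collects adherence to the supportive goal at weeks 3, 5 and 15. These could expose a problem. But the checklists and adherence measures are self-reported, duration says nothing about content, and none carries a threshold.
- **Contamination.** A reader might infer that section 12.4.1 drops the contamination deduction used in section 15. It is only silent on it, and the two texts can stand together.
- **Correlation.** The protocol never calls it agreement, and a constant over-report cannot hold at the ceiling of the scale. However, a coach who omits the same fraction of every shortfall never exceeds 100% and still gives r = 1.

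The conflicts over mode and topic are consistency errors, not evidence about sampling. They matter here only because the scored elements must be defined once.

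**Conclusion.** The point holds as a weakness of stated rules, not as proof that failure would go unseen. A pooled 90% average is insensitive to poor communication-skills delivery. At f0 = 98% it tolerates fidelity down to about 18% (10% share) or 45% (15% share). The result depends on f0: at 95% the limits are 45% and 62%, and at 92% the pooled rule performs much better. A monthly average is more sensitive, but it acts late and can trip when every session type is at 95%; under either window a trigger does not point to the session type at fault. The monthly results also rest on 10 independent elements per session and no dropout.

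Pearson correlation may be reported, but alone it does not establish that the coach's checklist is accurate. The contradictions over weeks 3, 5 and 15 are real. These changes should be made, since they cost almost nothing and bear on how a null difference is read.

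**What to change.** 1. State the averaging window. Compute fidelity for communication-skills sessions separately and apply the 90% trigger to that figure as well as overall.
2. Set a minimum number of communication-skills reviews per period, within the same total. For illustration, accrual takes 132 / 8 = 16.5 months; with 24 weeks of follow-up, sessions span about 22 months. That is 198 / 22 = 9 communication-skills sessions and 1,980 / 22 = 90 sessions in all per month, with 9 reviews. Ten communication-skills reviews per half-year would be 10 of 54, leaving 44 routine reviews instead of about 49. Ten per quarter would be 10 of 27, leaving 17 instead of about 24. If these sessions are oversampled, weight the overall average back to their true share.
3. Report contamination elements found in control sessions as a separate rate.
4. Replace or supplement Pearson with item-level percent agreement or kappa, and the mean coach-minus-reviewer difference.
5. Reconcile the mode of weeks 3, 5 and 15 (section 6.1.2 against sections 1, 3.1 and 7.11) and the control topics of weeks 3 and 5 (section 6.1.2 and the Visit 4 and 6 headings against section 7.7), so that the required elements are defined once.

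The cost is wording, a little extra tabulation and fewer reviews of routine lifestyle sessions: slight over a half-year window, larger over a quarter.
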